#### Autistic students

Two hundred students ages 8–14 years currently being served on an Individualized Education Plan (IEP) under any educational designation will participate. Recruitment will be prioritized within historically underserved communities given longstanding disparities in access to mental health care. Students will be included if they have: (1) a known medical diagnosis of autism, an educational identification of autism, OR suspected autism; AND (2) clinical anxiety according to either student, parent or teacher report. Students with suspected autism will be included if they have clinically significant impairment (T-score above 70) in reciprocal social behavior according to the Social Responsiveness Scale – Second Edition (SRS-2) [38] or if they exceed the cut-off score on the Social Communication Questionnaire, Lifetime Version (SCQ) [39] or the Autism Diagnostic Observation Schedule, Second Edition (ADOS-2) [40] administered by the research team. Clinical anxiety will be determined by: (1) significant elevation on the Total Score of the parent or child report of the Screen for Child Anxiety and Related Emotional Disorder (SCARED) [41]; (2) meeting or exceeding the cut-off for any of the subscales of the parent or child report of the SCARED; or (3) clinical elevations on the School Anxiety Scale – Teacher Report (> 17; SAS-TR) [42]. Students will be excluded if they have (1) known intellectual disability; (2) significant behavior or psychiatric challenges that prevent them from participation in small group activities; (3) lack of parent or caregiver permission for participation; or if students are: (4) actively receiving CBT targeting anxiety within the community. Students with intellectual disabilities will be excluded from the current trial because the cognitive and linguistic demands of the interventions are not tailored for youth with more significant learning challenges.

#### Caregivers

Two hundred caregivers of students 8–14 years defined above will be included. Participating caregivers will be asked to complete survey measures for their child and the PARS-ASD, participate in one parent contact, and complete surveys, the PARS-ASD, and exit interviews following their child’s participation in either ZOR or FYF-SB.

#### Measures

All measures will occur at baseline, post-treatment, and 6-month follow-up. Semi-structured interviews will also be conducted with a purposive sample of students, caregivers, and school providers. See Table 2 for a timeline of enrollment, study procedures, and measures.

**Table 2 Tab2:**
[figure not shown]
Schedule of enrollment across study time period

^**^t_1:_ Pre-FYF-SB/ZOR; t_2_: Post-FYF-SB/ZOR; t_x_: 6-month follow-up

### Student measures

#### Demographic Information

Caregivers will complete demographic information about their participating child and family. This includes the child’s age, race, ethnicity, grade and school placement, developmental and medical diagnoses, and school and community service history. Caregivers will also provide their own age, gender, race, ethnicity, highest educational obtainment, annual household income, household size, marital status, occupation, and the extent to which they experience psychosocial stressors such as food, housing, transportation, and healthcare related insecurities.

Primary outcome. screening for childhood anxiety and related emotional disorders – child/parent versions (SCARED) [41]*.* The SCARED is a 41-item inventory of statements that assesses five types of anxiety experienced by children and adolescents, to be completed separately by caregivers and students pre/post intervention and at 6 months follow-up. A total score, as well as cutoffs for specific domains of anxiety (e.g., social, generalized) are obtained. A total score of 25 or higher is clinically significant. Youth who obtain a score above the clinical cutoff for the total score or for 1 or more domains are eligible. The SCARED has been used in previous FYF-SB trials as well as in other studies with autistic children [24, 28]. Results from our previous research confirm the 41-item measure’s five-factor structure and suggest good sensitivity (0.71) and specificity (0.67) among parents of autistic youth [28].

Co-primary outcome. pediatric anxiety rating scale-autism spectrum disorder (PARS-ASD) [43]. The PARS-ASD is a clinician-rated semi-structured interview assessing anxiety severity and impairment over the past week, modified for autistic youth ages 5 to 17 from the original Pediatric Anxiety Rating Scale (PARS) [44]. The PARS-ASD will be administered by an independent evaluator (IE) masked to condition. It includes a Symptom Checklist and five Severity Items. The Symptom Checklist covers social anxiety, separation anxiety, generalized anxiety, panic, specific phobia, and other anxiety symptoms. The severity of symptoms is examined by assessing the frequency and pervasiveness of anxiety, as well as the extent to which the child avoids anxiety provoking situations (e.g., behavioral manifestations of anxiety). Interference with family relationships within the home and interference with peer and adult relationships and/or performance outside of the home are also examined. Preliminary psychometrics were strong: internal consistency was 0.90; convergent validity was supported, as the PARS-ASD was strongly correlated with other parent-reported anxiety measures (*rs* = 0.62–0.68); divergent validity was also supported as the PARS-ASD had low correlations with parent ratings of social withdrawal, stereotyped movements, hyperactivity and repetitive behaviors [43].

Stakeholder identified outcomes. In previous research studies, stakeholder partners listed the following as meaningful treatment outcomes within schools: number of tardies, attendance, grades, number of elopements (leaving school area without permission), amount of classroom participation, number of expulsions and suspensions, number of visits to the principal and nurse, use of coping strategies, increase in self-advocacy, number of phone calls home, number of referrals to the social worker, increase in social initiations with others, and decrease in outbursts [26]. We will operationally define these outcomes and partner with school teams and school personnel to collect each of these outcomes on participating students from the academic year prior to study participation and the academic year in which students participated in FYF-SB or ZOR.

Emotion dysregulation inventory (EDI) [45]. The EDI is a parent report measure of emotion dysregulation in autistic youth and will be completed pre/post intervention and at follow-up. The EDI can be used as a self-report measure and can also be completed by school providers. Items are rated on a 5-point Likert scale ranging from 1 (not at all) to 5 (very severe). The Reactivity short form (7 items) and Dysphoria factor (6 items) have demonstrated good internal consistency in autistic youth (Chronbach’s alpha = 0.92 for Reactivity Short Form; Chronbach’s alpha = 0.90 for Dysphoria).

The school anxiety scale, teacher report (SAS-TR) is a 16-item teacher-reported measure of anxiety designed to assess the behavior of children at school from 5 to 12 years of age [42]. Items are answered on a four-point scale. The measure provides a total score for anxiety (scores ranging from 0–48). It includes two subscale scores (reflecting social anxiety and generalized anxiety). The SAS-TR will be administered pre/post intervention and follow-up. This measure has been used in our previous school-based trials as well as in other school-based research with autistic students [21]. Internal consistency for both the total anxiety score (Cronbach’s alpha = 0.93) and the subscales (Cronbach’s alpha = 0.92) were strong. Test–retest reliability (intra-class correlations (ICC) ranged from 0.73-0.81) was also strong. Finally, convergent and discriminant validity were also good (0.76; -0.16; respectively).

Strengths and difficulties questionnaire (SDQ) is a 25-item teacher, parent and student reported tool measuring prosocial behavior and psychopathology of youth 3–16 years old [46]. The SDQ evaluates five-factors: emotional symptoms, conduct problems, hyperactivity/inattention, peer relationship problems, and prosocial behavior. Studies on the psychometrics of the SDQ have yielded satisfactory internal consistency (mean Cronbach’s α: 0.73), cross-informant correlation (mean: 0.34) and retest stability after 4 to 6 months (mean: 0.62). The SDQ has also been successfully used in autism research [47]. It will be administered pre/post intervention and at follow-up.

### Implementation measures

ISP demographic information. ISPs will indicate their age, race, ethnicity, gender identity, and disciplinary background. They will also indicate their years of experience working within their professional role, working with autistic students, and working with autistic students who have co-occurring anxiety.

Evidence-based practices attitudes scale (EBPAS) is a 15-item measure of providers' attitudes towards adopting novel, evidence-based practices [48]. It contains the following subscales: Requirements; Appeal; Openness; Divergence. Providers will rate the extent to which they agree with statements using a 5-point Likert scale with a 0 indicating “not at all,” and a 4 indicating, “to a very great extent.”

School Provider Stress and Burnout. ISPs will complete the 5-item Emotional Exhaustion subscale of the Organizational Social Context Questionnaire [49] to capture the fatigue and stress dimension of burnout. Each ISP will report their level of agreement on a 5-point Likert-type scale (1 = Strongly disagree to 5 = Strongly agree) to statements about their sense of emotional exhaustion from their work (e.g., “I feel burned out from my work.”).

Implementation leadership. ISPs will rate the extent to which their school supervisors are providing leadership in the use of EBPs using the 12-item Implementation Leadership Scale (ILS) [50]. The ILS assesses a leader’s behavior with regard to EBP implementation across four main domains: proactive, knowledgeable, supportive, and perseverant. ISPs will rate each item using a 5-point Likert scale with a 0 indicating “not at all” and 4 a “very great extent.” Past research has demonstrated that the ILS has excellent internal consistency, as well as convergent and discriminant validity (Aarons et al., 2014). It has also been used in other school studies for autism with strong internal reliability (Williams et al., 2021).

Implementation climate. ISPs will rate their school’s evidence-based practice (EBP) implementation climate using the Implementation Climate Scale (ICS) [51]. The ICS includes 18 items rated on a Likert scale from 0 (not at all) to 4 (very great extent). Items are averaged to produce a total score. Item content covers six domains, including focus on EBPs, educational support for EBPs, recognition for EBPs, rewards for EBPs, selection for EBPs, and selection for openness. The scale is psychometrically validated and has been used in other studies examining the implementation of autism EBPs within schools [51, 52].

Intervention fidelity*.* Two separate but similar treatment fidelity checklists will be used to document treatment adherence as well as provider competence in delivering core components of FYF-SB or ZOR. The measures will assess the ISPs’ adherence to their assigned intervention by assessing the presence/absence of core components as well as the quality of intervention delivery. In ZOR*,* the checklist will measure ISPs’ adherence to the four key elements of preparation, provision of structure, quality of facilitation, and adult evaluation of student learning. In FYF-SB, the checklist will measure ISP’s adherence to core activities included within each session. It will also include an overall competence rating in which ISP’s Both FYF-SB and ZOR fidelity will be coded by trained research team members with reliability calculated on 15–20% of scored sessions.

Implementation survey. At the conclusion of delivering FYF-SB or ZOR, ISPs will rate the feasibility, acceptability, and appropriateness of their respective intervention, including the likelihood that providers will continue to implement the intervention once the study has ended. Providers will rate each of 36-items using a 5-point Likert scale. This survey was adapted from several different sources [53] and is designed to examine intervention feasibility, acceptability, and appropriateness for the school setting. An adapted version of this survey has been used in other studies examining the feasibility of interventions for autistic youth, including in our previous school trials [27, 28].

Acceptability questionnaires. A six-item acceptability questionnaire will be completed by participating students asking them to respond to questions such as “How much did you enjoy participating in FYF-SB/ZOR?” or “Do you feel better after participating in FYF-SB/ZOR?” Students will rate each item using a 5-point Likert scale.

Semi-structured exit interviews. A random subset of students, caregivers, and ISPs will be engaged in semi-structured exit interviews conducted by an independent member of the research team. For ISPs, the exit interviews are designed to understand the acceptability, appropriateness, and feasibility of FYF-SB and ZOR, as well as the implementation outcomes of the intervention in which they were trained*.* Interview questions for ISPs will include: 1) overall impressions of the intervention; 2) relative advantage of FYF-SB or ZOR; 3) the feasibility of implementing the intervention; 4) adaptations necessary to support intervention implementation; 5) the perceived impact of the intervention on anxiety outcomes; and 6) the extent to which the intervention will be used in the future. For caregivers and students, interview questions include: 1) overall impressions of FYF-SB or ZOR; 2) the acceptability of the intervention; 3) how FYF-SB or ZOR compared to other mental health interventions received; 4) the impact of FYF-SB or ZOR on anxiety and emotion regulation outcomes; 5) the extent to which caregivers were involved in the intervention and saw skill generalization at home; and 6) whether the caregiver or student would recommend the intervention to others. All interviews will be audio-recorded, transcribed verbatim and de-identified.

### Analytic plan

Between-arm imbalance of baseline characteristics will be examined using* t* and chi-square tests and evaluated based on summary statistics. Intervention effect of FYF-SB as compared to ZOR will be assessed using Linear mixed effect model (LMM) for continuous outcomes and non-linear mixed effect model (NLMM) for categorical outcome such as school attendance. To account for the design effect of clustering trials, random school (cluster) effect will be in the models for outcome without repeated measures while appropriate covariance structure of LMM/NLMM accounting for both the design effect and the correlation of repeated measures will be used for outcome with repeated measures. Transformation of outcome (i.e., Square root or log) will be used if normality assumption is violated. Any imbalanced potential confounding variables will be adjusted for modeling. Primary analysis will be conducted on intent-to-treat basis (ITT). LMM and NLMM will be the primary method for dealing with missing values without data imputation since missing patterns would most likely be of the missing at random (MAR) pattern. The change score from baseline to the end of intervention is considered to the primary effectiveness endpoint. No type I error adjustment for multiple tests in a single model or multiple outcomes will be applied. *P* < 0.05 is deemed statistically significant. No interim analysis will be performed. To examine the robustness of primary analyses, sensitivity analyses will be conducted, including the same analyses among completers and analyses after missing data are imputed using Markov chain Monte Carlo method.

#### Aim 1

The SCARED and PRAS-ASD are the co-primary outcome variables. Both primary and secondary outcomes will be analyzed using the above discussed LMM/NLMM model with fixed effects consisting of time (i.e., baseline/end of treatment/6 months follow-up), comparator (FYF-SB or ZOR) and their interaction. Intervention effect of FYF-SB as compared to ZOR will be estimated by between-comparator difference in the change score of outcome measure from baseline (i.e., interaction) with 95% confidence interval and be tested statistically under the statistical model.

#### Aim 2

Quantitative data will be analyzed in the same fashion as for the outcome without repeated measures in Aim 1. Consistent with CORE-Q reporting guidelines [54], all interviews will be audio-recorded, and transcribed verbatim. ​​Exit interview data will be formally analyzed using conventional content analysis [55, 56]. This form of analysis is commonly used in studies with the aim of describing a phenomenon at a level that closely reflects the transcript content. In the case of Aim 2 data, the content analysis will be used to closely describe stakeholder perspectives of the feasibility (i.e., ease of use), acceptability, and appropriateness of FYF-SB or ZOR, as well as the infrastructure necessary to implement and sustain these programs. All coding will be facilitated by MAXQDA software. Additionally, all qualitative results will be member checked with our stakeholder advisory board members prior to synthesis into various products.

#### Aim 3

To explore the impact of baseline symptoms and other demographic variables on the intervention effect, we will include similar models to those being tested in Aim 1, with the use of an interaction term (i.e., intervention x moderator x time interaction) in addition to related two-way interaction terms. Candidate moderators, including age, will be examined. If an interaction results in significance, we will further test treatment effects within subgroups analogous to hypotheses in Aim 1. Similar analysis will also be conducted with the outcome dichotomized as responder and non-responder using clinical criteria.

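### For Aim 2 outcomes measured once after delivery, the mixed model analyses responders only, so the stated missing-data method gives little protection; prespecified baseline covariates should replace the imbalance trigger.

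*Protocol article*

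**What the plan says.** All references are to the Protocol article.

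- **Missing data (Analytic plan).** "LMM and NLMM will be the primary method for dealing with missing values without data imputation". The reason given is an expectation that values will be missing at random. A completers analysis and Markov chain Monte Carlo imputation are planned as sensitivity analyses.
- **Model for outcomes measured once (Analytic plan).** "random school (cluster) effect will be in the models for outcome without repeated measures". No covariate is named. The rule for covariates is: "Any imbalanced potential confounding variables will be adjusted for modeling".
- **Aim 2.** "Quantitative data will be analyzed in the same fashion as for the outcome without repeated measures in Aim 1".
- **Timing of the two outcomes (Implementation measures).** For providers: "At the conclusion of delivering FYF-SB or ZOR, ISPs will rate the feasibility, acceptability, and appropriateness of their respective intervention". For students: "A six-item acceptability questionnaire will be completed by participating students"; the sample items ask about a programme already received.
- **Provider data that might help (Implementation measures).** Years of experience, attitudes to evidence-based practice (EBPAS), implementation leadership and climate, and burnout: "ISPs will complete the 5-item Emotional Exhaustion subscale of the Organizational Social Context Questionnaire".

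**The concern.** A likelihood-based mixed model handles values missing at random through what it conditions on: the person's other measurements and the covariates in the model. For the repeated Aim 1 outcomes, the baseline value of the same scale does that work. The two Aim 2 outcomes have no baseline value, and the only stated fixed structure is arm plus a random school effect. The missing-data statement, read together with the Aim 2 sentence, therefore suggests more protection than this model can give.

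Aim 2 compares acceptability, appropriateness and feasibility between the programmes. If providers with poorer attitudes or more exhaustion return the survey less often, and this happens more in one arm, that arm's responders look too favourable. The Background gives a reason why loss might differ: it describes graded exposure, which Table 1 lists only for FYF-SB, as often new to school providers and possibly hard to organise in schools. Covariates that could correct for this enter only if they look imbalanced between arms. That criterion has nothing to do with whether they predict the rating or its absence.

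**Working it through.** The plan gives no loss rate and no power figure for Aim 2. Its only power figure concerns the SCARED and plays no part here.

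**1. Does the model use non-responders?** A random-school model was fitted to one simulated data set with 67 of 200 outcomes missing, then again with those 67 rows deleted. Estimate (0.434) and standard error (0.193) were identical. A schoolmate's rating is the only indirect help. At ICC 0.15, the top of the range in the sample-size section, it changed the arm contrast by at most about 0.002 SD against the raw responder difference.

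**2. Size of bias when missingness depends on a baseline covariate.**

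Assumed inputs, none of them in the protocol:
- covariate x is standard normal and correlates r with the rating; the rating has SD 1
- no true arm difference
- probability of a missing survey = expit(a − x), with a = −1.00 in one arm and a = −2.55 in the other

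Numerical integration gives 30.3% and 10.1% missing. The mean of x among responders is 0.255 and 0.092.

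Bias = r × (0.255 − 0.092) = 0.163 r

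| r | formula | simulated random-school model | with x as covariate |
|---|---|---|---|
| 0.3 | 0.049 | 0.051 | 0.002 |
| 0.5 | 0.082 | 0.083 | 0.000 |
| 0.7 | 0.115 | 0.115 | −0.001 |

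A separate simulation used 200 providers in 100 schools, school ICC 0.1, nominal loss of 10% versus 25-35%, and a missingness odds ratio of 2-3 per SD. It gave 0.03-0.05 SD at r = 0.3 and 0.05-0.11 SD at r = 0.5. The bias favours the arm with more loss.

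**3. Against sampling error.** Take 100 providers per arm, so about 90 and 70 responders, and a design effect of 1.15 (2 per school, ICC 0.15). The standard error is √(1.15 × (1/90 + 1/70)) = 0.171 SD. A bias of 0.082 is then 0.082 / 0.171 = 0.48 of a standard error.

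**4. When there is no bias.** It is zero within simulation error (0.002 or less) if loss is 10% versus 30% but completely random, or if loss of about 20% depends on x in the same way in both arms. In the second case responders are selected in each arm, but the selection cancels in the contrast.

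**5. A less favourable pattern.** If missingness depends on x only in the 30% arm and is random in the other, bias = 0.255 r: 0.077, 0.128 and 0.179 SD at r = 0.3, 0.5 and 0.7 (simulated 0.074, 0.132 and 0.181). Adding x again brings it to about zero.

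**6. When non-response depends on the rating itself.** At 10% versus 30% loss, the bias is 0.16-0.17 SD. Adding x reduces it only to 0.15, 0.13 and 0.09 SD at r = 0.3, 0.5 and 0.7. At 10% versus 35% and r = 0.5, it falls from 0.18 to 0.14.

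**7. Precision at equal loss.** Adjustment cuts the variance of the contrast by about 6-8% at r = 0.3 and 19-24% at r = 0.5.

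**The case against.** The strongest objections, and what stands of each:

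- **The missing-data sentence is mainly about Aim 1.** It sits next to the intent-to-treat statement and the change-score endpoint, and for the repeated outcomes it is sound. Nowhere does the protocol say that the model protects the end surveys from non-response. This is fair. The sentence reaches Aim 2 only because Aim 2 is to be analysed in the same fashion, so the point is that protection there is small, not that the protocol makes a false claim.
- **A reader might infer that the analysis is valid only if, within each arm, non-response is unrelated to the rating.** That is too strict for a contrast, as step 4 shows.
- **A reader might infer that covariates would cure the most intuitive problem, dissatisfied people not answering.** They would not. That is dependence on the rating itself, and step 6 shows only partial correction.
- **The provider scales may not be true baseline data.** Under Procedures, providers are consented after their school is randomised and are then trained in the assigned programme. The scale descriptions give no timing, the schedule table is not shown, and the general statement that all measures occur at three times cannot be literal for an end-of-delivery survey. Scales completed after that training could be affected by arm. This stands and limits the fix.
- **The student part is weaker.** Student self-report is collected in person by research staff, which makes selective non-return less likely. The simulations concern providers, and nothing in the protocol shows that age or SCARED predicts acceptability. This stands.
- **Imputation is already planned, and covariate lists are detail for an analysis plan.** Making imputation primary for a secondary aim would be a preference, and the protocol gives no ground for insisting on it. What remains is a rule that the protocol does fix: covariates enter only on observed imbalance. The completers analysis adds little here, because it is essentially the same analysis.

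**Conclusion.** The point holds in a limited form. For the provider survey and student acceptability, the planned model is in effect an analysis of responders, and the stated missing-data method gives little protection. Bias in the arm contrast needs non-response that both relates to the rating and differs by arm. Under assumed loss of 10% versus 25-35% driven by baseline characteristics, it is about 0.03-0.1 SD. It is larger if the dependence exists in one arm only or the correlation is high, and zero if loss is random or follows the same pattern in both arms.

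The loss rates, correlations and missingness models are all assumptions. A reader might conclude that the Aim 2 comparison is biased, or that the trial's main result is in doubt. The documents support neither: they give no evidence on survey return, Aim 2 is a secondary aim, and the SCARED and PARS-ASD are measured repeatedly.

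**What to change.** For outcomes measured once, replace adjustment triggered by imbalance with a short prespecified set of baseline covariates already collected:

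- **Providers:** years of experience; add EBPAS, emotional exhaustion, leadership and climate scores only where they were completed before training in the assigned programme.
- **Students:** age and baseline SCARED.

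State that these outcomes are analysed on responders, report survey return by arm, and keep multiple imputation using these variables as the sensitivity analysis.

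The cost is wording and a little extra analysis, with no new data. It uses a few degrees of freedom, and missing covariate values need simple imputation. The gain depends on how strongly the covariates predict the rating, and correction is only partial if non-response depends on the rating itself.

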### Sample size and power analysis

This study was primarily powered on detecting a between-comparator difference in the primary outcome (i.e., SCARED score) using ITT analysis. We expect the mean cluster size across the 100 schools to be 2 participants, ranging 2–5. Based on the FYF-SB RCT [28], estimates of ICC ranging from 0.001–0.15 were conservatively used in this power analysis. Our study will have 80% power at 5% significance level, with 100 participants per arm to detect a medium effect size (0.45 of Cohen’s D). Additionally, studies with autistic youth that each compared two active treatments further supported our anticipated effect size and power. Two studies reported significant treatment effects when comparing CBT adapted for autistic youth to other interventions (Standard CBT; Enhanced Standard Community Treatment) [57, 58]. The effect size when comparing these two active comparators was medium in size (ranging from 0.50- 0.63) [57, 58]. The effect sizes from these two studies are nearly equivalent to the effect size used for our current study, given that all are within the medium category according to effect size interpretation [59]. We will also have sufficient power to detect the medium effect size for the secondary outcomes.

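### The primary model estimates an unadjusted difference in change from baseline, which is valid but less precise than adjusting for the baseline score already collected

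*Protocol article*

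**What the plan says.** The Analytic plan names the endpoint: "The change score from baseline to the end of intervention is considered to the primary effectiveness endpoint". Under Aim 1 the mixed model has "fixed effects consisting of time (i.e., baseline/end of treatment/6 months follow-up), comparator (FYF-SB or ZOR) and their interaction", and the intervention effect is "estimated by between-comparator difference in the change score of outcome measure from baseline (i.e., interaction) with 95% confidence interval". The baseline score is therefore one of the outcome rows, not a covariate, and the comparator main effect lets the two arms have different baseline means.

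The only covariate adjustment named depends on the data: "Any imbalanced potential confounding variables will be adjusted for modeling".

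The baseline score is collected in any case. The Student measures section describes the SCARED as "to be completed separately by caregivers and students pre/post intervention and at 6 months follow-up", and the Caregivers section has the PARS-ASD completed before and after the intervention.

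The Sample size and power analysis section claims "80% power at 5% significance level, with 100 participants per arm to detect a medium effect size (0.45 of Cohen’s D") for school ICCs of 0.001 to 0.15 and a mean of 2 students per school. It gives no baseline-to-post correlation, does not say which SD the 0.45 refers to, and takes no credit for baseline adjustment.

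**The concern.** A difference in change gives the baseline score a weight of exactly 1. Baseline adjustment gives it the weight at which it predicts the later score, which is usually below 1. Subtracting the whole baseline when only part of it carries forward adds noise. It also over-corrects a chance baseline difference: the arm that happens to start with higher anxiety will tend to show a larger fall.

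What is at stake is precision. The sample is fixed at 200 students, and both comparators are active programs described as rooted in CBT principles. The analysis model is therefore one of the few cheap places to narrow the confidence interval.

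**Working it through.** **1. The plan's own power figure.** Inputs (Sample size and power analysis): 100 per arm, d = 0.45, 5% level (two-sided assumed), mean cluster size 2, ICC 0.001 to 0.15. Design effect = 1 + (2−1)×ICC.
- ICC 0.15: effective n = 100/1.15 = 87.0; SE = √(2/87.0) = 0.152; power = Φ(0.45/0.152 − 1.96) = 84.3%.
- ICC 0.001: effective n = 99.9; power = 88.9%.

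The stated 80% is on the cautious side of these figures. It is met at ICC 0.15 with, for example, 10% dropout (80.4%).

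**2. What the planned model estimates.** With baseline as a level of time, and arm, time and arm-by-time all free, the interaction with complete data equals the difference in mean change. An exact generalized least squares calculation (100 schools of 2 students, three visits, ρ = 0.5, ICC 0.001) gives variance 0.0200, the change-score variance. With a common baseline mean it is 0.0150, a ratio of 0.75.

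**3. Size of the loss.** With equal SDs, set to 1, at baseline and post:
- change score: variance proportional to 2(1−ρ)
- baseline-adjusted: variance proportional to 1−ρ²
- ratio: (1−ρ²)/[2(1−ρ)] = (1+ρ)/2

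ρ is an assumption. The nearest figure in the article is the SDQ's "retest stability after 4 to 6 months (mean: 0.62"), which belongs to a different instrument. At ρ = 0.62 the ratio is 0.81. The last column is Φ(2.80/√ratio − 1.96), starting from exactly 80%.

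| ρ | Ratio | SE reduction | Students for the precision that change scores get from 200 | 80% power becomes |
|---|---|---|---|---|
| 0.5 | 0.75 | 13% | 150 | 90% |
| 0.6 | 0.80 | 11% | 160 | 88% |
| 0.7 | 0.85 | 8% | 170 | 86% |
| 0.8 | 0.90 | 5% | 180 | 84% |

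**4. Clustering.** At ICC 0.15 the ratio at ρ = 0.5 is 0.75 if school effects share the students' correlation over time, and 0.78 if the school effect is constant over time. At ρ = 0.7 it is 0.85 and 0.87.

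**5. From the trial's own inputs rather than exactly 80%, at ICC 0.15.** If d = 0.45 is on the SD of the score, power moves from 0.84 to 0.93 (ρ 0.5), 0.91 to 0.96 (0.6) and 0.97 to 0.99 (0.7). If it is on the SD of the change, 0.84 becomes 0.93, 0.91 and 0.90 for the same ρ.

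**6. Unequal SDs through selection.** Suppose 0.62 is the regression slope in an unselected population and enrolment on elevated scores cuts baseline variance to a fraction k. The adjusted variance is 1 − 0.62² = 0.6156, and the change variance is 0.6156 + (1−0.62)²k.
- k = 0.7: 0.6156/0.7167 = 0.86
- k = 0.5: 0.6156/0.6878 = 0.90

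The SE saving falls to 7% or 5%, and 80% power becomes about 86% or 84%.

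**7. Chance imbalance.** With no treatment effect, a baseline difference Δ predicts a post difference of ρΔ, so the change difference shifts by −(1−ρ)Δ. One standard error of baseline imbalance, ignoring clustering, is √(2/100) = 0.141 SD. Over ρ 0.8 to 0.5 this shifts the change difference by 0.2×0.141 = 0.03 to 0.5×0.141 = 0.07 SD.

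**The case against.** The strongest reply is that nothing here is stated wrongly. The difference in change is a standard estimator with correct type I error, and the power section neither assumes baseline adjustment nor fails without it. This stands, and it makes the point an improvement in efficiency rather than a correction.

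A reader might infer that regression to the mean biases the comparison, because students enter on elevated scores on a scale that is also the outcome. The documents do not support that. The same eligibility rule applies in both arms, so regression to the mean cancels in expectation. Eligibility is also broader than the outcome scale: under Autistic students, a SCARED total or subscale from parent or child, or the teacher-rated SAS-TR, can qualify a student. Nor does a chance imbalance pass in full into the result; about (1−ρ) of it does, and it averages out over randomizations.

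A further reply is that the imbalance clause already covers baseline. It does not do so reliably. It is triggered by the observed data, and it does not say how a baseline score that is already an outcome row would be adjusted for.

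Two cautions also stand. First, ρ for the SCARED and PARS-ASD is unknown, and selection can shrink the gain. Second, the Procedures section has trained providers nominate students after their school is randomized. Arms may therefore differ systematically at baseline. In that case the two analyses can estimate different quantities, and neither fully removes the bias.

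**Conclusion.** The point holds as one of precision. As written, the primary analysis is an unadjusted difference in mean change, and its variance exceeds that of a baseline-adjusted analysis by a factor of 2/(1+ρ) when SDs are equal. For an assumed ρ of 0.5 to 0.8, adjustment cuts the standard error by 5 to 13% and would lift an analysis at exactly 80% power to about 84 to 90%. If selection narrows baseline variance, the gain sits toward the lower end.

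It would go too far to call the planned estimator invalid, the comparison systematically biased, or the trial underpowered for this reason. The stated 80% is not wrong and does not rest on the choice. The change is worth making because the data are already collected.

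**What to change.** Before outcomes are examined by arm, prespecify for each co-primary score a linear mixed model with:
- the post-treatment and 6-month scores as the repeated outcomes
- arm, visit, arm-by-visit, baseline score and baseline-by-visit as fixed effects
- the planned handling of school clustering

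The primary estimate is the adjusted arm difference at end of treatment, with its 95% confidence interval. Entering baseline as a covariate is preferable here to a model that forces equal baseline means, because students are nominated after school randomization. Keep the planned difference in change as a sensitivity analysis for the same reason.

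The cost is mostly wording, with no new visits, data or students. Two details need attention. A student with a missing baseline stays in the planned model but drops out of this one, so a simple rule for missing baselines is needed, reconciled with the plan's intention to run the primary analysis without imputation. This matters more for the PARS-ASD, which is not an eligibility measure. The Aim 3 moderator models, which reuse the Aim 1 structure, need matching wording.
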